### Recruitment of patients

Hospital notes are initially checked to identify eligible patients. The patient's consultant confirms their eligibility in terms of clinical conditions related with mobility. The study objectives, hypotheses, design and data collection procedures are then discussed with patients who meet the inclusion criteria. They are given an information sheet to read at home and are then phoned within 3-5 days to get their verbal consent to participate in the study. An appointment date is arranged for collection of baseline data at the clinic. Prior to the visit, a set of self-administered questionnaires are mailed to the patient for completion and they are asked to bring the completed questionnaires to their next visit. Patients provide written consent on the day of recruitment; before data collection. Midterm and final assessment dates are then scheduled for a 3 month (13 weeks) and 6 month (25 weeks) follow-up visit (Figure 1).

### Randomisation

Patients are randomised using a block randomisation approach with computer generated random numbers, to the intervention and control group, with equal probability that they are randomised to the intervention or control arm. Using a block size of four there are six sequence permutations to which we can allocate patients to the intervention (I) and control (C) arms: IICC, ICIC, ICCI, CIIC, CICI, and CCII. One of the six permutations was selected randomly and then four patients assigned accordingly. The process was repeated to allocate patients to the intervention and control arms for the required sample size. An independent researcher constructed the allocation sequence and sealed these in individual opaque envelopes with study identification numbers on the front. Patients are only numbered once they have provided verbal consent by phone. Randomisation takes place at an individual level after the baseline measurements have been taken and approximately one week prior to the start of the intervention. Therefore, the researcher does not know the allocation of the patients until the baseline data collection has been completed. Similarly patients are consented to the study before they know which group they will have been allocated to.

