## Method

### Design

Patients are randomised either to receive the dietary modification and physical activity intervention or standard care (control group) with a 1:1 allocation ratio (Figure 1).

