### Sample size

This study is an exploratory one and so formal power calculations are difficult. The primary endpoint used to calculate sample size was body composition. Smith *et al *[17] presented data from a study of prostate cancer patients treated with hormone therapy and the mean percentage change in fat mass following ADT treatment was 9.4% (SD = 9.6%). If it is assumed that the controls in the planned study will have a similar percentage of fat mass, then with 36 patients in the intervention group and 36 patients in the control group the study will have 90% power at 5% significance to detect a mean percentage change in fat mass of 7.4% between the control and intervention group. An additional 30% was added to the sample size calculation to account for non-compliance and potential drop-out or discontinuation. Therefore 47 patients will be randomised to the intervention and 47 randomised to the control group. This sample size will also allow us to detect a 3.4 point (SD = 5.0 points) difference in Fatigue Severity Score [8] (a 3 point difference on the fatigue scale is considered to be the minimal clinically important difference) [18]; and a 6.0 point (SD = 9.0 points) difference on the Functional Assessment of Cancer Therapy-General (FACT-G) score [8].

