### Quality control

Following the initial visit, patients are contacted by phone every 2 weeks for the first 3 months and every 3 weeks thereafter to monitor progress and compliance with the intervention and to record any possible adverse events. The control group is also contacted every 6 weeks, for a general discussion about their condition. To standardise the follow-up call a written check-list has been used and relevant information (walking steps from the previous week and their goal for the current week, illness etc.) are collected. Each participant is encouraged to bring their partner or care-giver on the day of data collection and to be present for the nutritionist's visit at their home to help to answer questions regarding dietary intake and food preparation for those who may not be actively involved in food shopping and cooking. It is also hoped that by involving the patient's partner/care-giver, the patient is encouraged to comply with the intervention at home. The baseline and follow-up (3 month and 6 month) body composition measurements are completed by the same person to avoid inter-interviewer bias. However, this person is not masked to treatment assignment. Although it is preferable to have any subjective measurements, such as body composition measurements, taken by a person who is masked to treatment allocation, this was not possible in the present study and in order to minimise any bias that may be introduced, all body measurements are taken and recorded without referring to the previously recorded measurements.

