The majority of ADT treated prostate cancer patients are overweight and obese [42]. Though we are not promoting a weight reducing diet, and weight reduction is not the primary goal of the intervention, it is likely that an improvement in dietary intake and a higher level of physical activity will result in modest weight loss in the intervention group. It is known that overweight and obesity is associated with an increased risk of chronic diseases including cardiovascular disease, diabetes, some forms of cancer and recurrence of cancer. Therefore, maintenance of weight or gradual weight loss in the intervention group can be viewed as a favourable outcome [43]. Because our intervention incorporates both dietary modification and physical activity, we will not be able to separate out the effects specifically attributable to either of these components. Furthermore, with no allocation concealment the control group patients will be free to change their diet and increase their physical activity; even though such behaviour may weaken any observed associations in the intervention arm.

The external validity of the study will depend on the representative of the patient population from which we recruit and on the proportion of eligible patients who agree to participate in the study. For logistic reasons, recruitment is limited to one centre, which is the regional oncology centre (in Belfast) and patients treated within this centre may not be representative of all prostate cancer patients treated with ADT. Also, the characteristics of recruited patients may be influenced by the study design e.g. patients who agree to take part in the trial may be more likely to be older or retired or highly motivated, as involvement in the study demands three additional clinic visits for outcome measurement. Patients living outside of the Belfast area may be more likely to decline in order to avoid more frequent journeys to the clinic and the associated additional costs that may be incurred. However, we are making every effort to arrange our follow-up visits to coincide with the patients' 3-monthly follow-up visits with their consultants to minimise travel. A positive aspect of our approach to recruitment is that potential participants have to be initially approached by their consultant which may lead to a better uptake than other approaches to recruitment e.g. community advertisement [44].

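### A single fixed block of four, with study numbers given before baseline and an unmasked measurer, does not assure the concealment that the Randomisation section infers from opening envelopes after baseline

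*Protocol article*

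**What the plan says.** All references are to the protocol article.

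- **Block structure (Randomisation).** "Using a block size of four there are six sequence permutations", all six are listed, and "One of the six permutations was selected randomly and then four patients assigned accordingly". The step is repeated until the sample is reached. No other block size, random variation of size or stratification is mentioned.
- **Ratio, size and centre.** Design gives allocation "with a 1:1 allocation ratio". Sample size says: "Therefore 47 patients will be randomised to the intervention and 47 randomised to the control group". Patients come from one centre (Setting and participants; Discussion).
- **Concealment device (Randomisation).** An independent researcher built the sequence and sealed it in opaque envelopes labelled with study numbers. "Patients are only numbered once they have provided verbal consent by phone". Allocation follows the baseline measurements, and from this the section concludes that "the researcher does not know the allocation of the patients until the baseline data collection has been completed".
- **Masking (Quality control).** The same person takes the body measurements at baseline, 3 and 6 months. "However, this person is not masked to treatment assignment".
- **Discussion.** The article also says that "with no allocation concealment the control group patients will be free to change their diet".

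**The concern.** The assurance in the Randomisation section is drawn from timing: the envelope is used after baseline, hence nobody knows the arm at baseline. Timing protects only the contents of that man's own envelope. In a balanced block of known fixed size, the earlier allocations constrain the later ones. The study number fixes a man's place in the block, and he holds it before his baseline visit. With one centre and no stated strata there is only one sequence to follow, and the person who measures body composition is not masked to the arms of men already in the trial.

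At stake is a baseline measurement taken by someone who may be able to work out the arm. Skinfold readings depend on the operator, and the Quality control section itself classes body measurements as subjective. The baseline value enters both the change score and the ANCOVA (Statistics), and body composition is the endpoint on which the trial was sized. The stated safeguard, measuring without looking at earlier readings, acts on follow-up visits and cannot protect the first one.

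**Working it through.** **Inputs.** Block size 4, ratio 1:1, one sequence (Randomisation; Design); 94 men (Sample size: 47 + 47). The number of men who hold a study number but whose envelope is still unopened is not given, so it is varied below as an assumption.

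**Step 1: the plan's own figure.** Balanced sequences in a block of four: C(4,2) = 6. This reproduces the six listed.

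**Step 2: certain deduction when every earlier envelope in the block is open.** Count an allocation as deducible if every listed sequence that fits the earlier allocations gives the same arm.

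- 1st and 2nd positions: never.
- 3rd: only after II or CC, which is 2 of 6 sequences = 1/3.
- 4th: always.

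Per block: 0 + 0 + 1/3 + 1 = 4/3, so (4/3)/4 = 1/3 (8 of the 24 positions across the six sequences). For 94 men there are 23 full blocks plus 2 men, and those 2 are never deducible: 23 × 4/3 = 30.7 men, and 30.7/94 = 32.6%.

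**Step 3: best guess in the same setting.** By position the chance of a correct guess is 1/2, 2/3, 2/3 and 1. The mean is (0.5 + 0.667 + 0.667 + 1)/4 = 17/24 = 70.8%, against 50% by chance.

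**Step 4: overlap.** Leave the most recent one or two earlier envelopes unopened when the next man is measured.

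| Earlier envelopes unopened | Certain deduction | Men of 94 | Best guess |
|---|---|---|---|
| 0 | 1/3 (33%) | 30.7 | 70.8% |
| 1 | 1/12 (8.3%) | 23 × 1/3 = 7.7 | 58.3% |
| 2 | 0 | 0 | 54.2% |

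With one unopened, only the 4th position can be deduced, and only when the first two match: (1/3)/4 = 1/12.

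**Step 5: effect of varying the block size.** In 1,000 simulated trials of 94 men, a guesser knew the set of possible sizes and every earlier allocation, but not the size of the current block. Sizes were drawn with equal probability.

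| Scheme | Certain deduction | Best guess |
|---|---|---|
| Fixed 4 | 32.6% | 70.6% |
| 4 or 6 | 5.6% | 69.1% |
| 4, 6 or 8 | 2.2% | 68.0% |

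Varying the size removes nearly all certainty but only a little of the advantage in guessing.

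**Step 6: which outcomes are exposed.** Under Primary outcomes, fatigue and quality of life are self-reported, and Recruitment of patients says self-administered questionnaires are posted before the visit. The measurer has little means of influencing these. Body composition is taken by the unmasked person, and the 7-day activity recall is administered by an interviewer. These are the kinds of measure open to influence at baseline.

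**The case against.** The strongest reply is that one in three is a ceiling. It requires staff to know the block size, to track each earlier allocation by position, and to see men strictly one at a time. The article states none of these. That the block size is printed in the article does not show that recruiting or measuring staff had it during recruitment, since an independent researcher made the sequence. Overlap is plausible too: between phone consent and allocation come an appointment, posted questionnaires and a 7-day food diary, and a man lost after verbal consent could leave an envelope unopened. All of this stands, and it is why the result is a range from 0% to 33%.

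A reader might go further and infer any of three things that the documents do not support:

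- **That concealment fails.** An independent sequence in sealed opaque envelopes is described, and even in the worst case two thirds of allocations cannot be deduced with certainty.
- **That men were selectively booked.** The consultant confirms eligibility and makes the first approach, and numbers follow verbal consent. Nothing says that the measurer or nutritionist decides who enters.
- **That the Discussion admits there was no concealment.** The sentence there concerns control patients being free to alter their behaviour, so absence of blinding is evidently meant. It conflicts with the Randomisation section as worded, but it is a slip and not evidence about the envelopes.

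It is also fair to say that a fixed block of four is a common choice in a small trial that calls itself exploratory, and that the unmasked measurement is openly disclosed. Neither point repairs the inference from timing to concealment.

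**Conclusion.** The point holds in a limited form. Opening each envelope after baseline does not by itself ensure that staff cannot know the arm, so the Randomisation section's conclusion is unsupported as written. Concealment is not assured for up to 33% of allocations (about 31 of 94). The figure drops to 8% (about 8 men) with one earlier envelope in the block unopened and to 0% with two. It assumes that staff know the block size and the earlier allocations; the article confirms only that the body-composition measurer is unmasked.

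The exposure is mainly to baseline skinfolds, circumferences and interviewer-led measures. No effect on any trial result has been calculated, because the documents give no basis for one, and no actual subversion is suggested. This is an inexpensive improvement to the design together with two corrections of wording.

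**What to change.** 1. **Envelopes.** Have the independent researcher regenerate the unused envelopes with randomly varying block sizes, for example 4, 6 and 8, not disclosed to recruiting or measuring staff. Certain deduction falls from about 33% to about 2%; best-guess accuracy falls only from about 71% to 68%, so the unmasked measurement remains a limitation to report.
2. **Randomisation section.** Replace the conclusion drawn from timing with a statement of what is assured: a man's own envelope is unopened until his baseline is complete. Add who had access to the block size and to earlier allocations.
3. **Discussion.** Replace *no allocation concealment* with *no blinding of participants*.

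Moving the assignment of study numbers to after baseline is not recommended. It adds little when men enter one at a time, and where men overlap it could restore strict serial opening, which is the most predictable case.

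**Cost.** One new set of envelopes, and a possible final imbalance of a few men. Exact balance is not guaranteed now either: 94 = 23 × 4 + 2, and the first two places of a block differ in 4 of the 6 sequences, so 47:47 arises with probability 2/3 and 48:46 otherwise.

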### Intervention

Those patients randomised to the intervention arm receive the intervention from a qualified nutritionist. Within a week after their baseline measurements are taken, the nutritionist visits the patients at their home to describe and deliver the intervention which has two components; dietary modification and physical activity.

#### Dietary modification

The dietary advice is developed based on the patients' usual dietary intake, measured at baseline using a 7-day food diary. They are provided with individually tailored advice to encourage them to adopt a diet that is commensurate with current dietary guidelines [19] and, specifically, to meet the following criteria;

a) Eat 5 or more servings of vegetables and fruits per day

b) Reduce total fat intake to 30%-35% of total energy, with < 10% of energy from saturated fat

c) Limit polyunsaturated fat intake to 10% of daily total energy intake

d) Limit consumption of processed meats

e) Eat fibre-rich foods. Aim to consume 25 to 35 g of fibre daily

f) Limit alcohol intake ≤ 28 units/week

g) Limit intake of foods high in salt and/or sugar

#### Moderate physical activity

Brisk walking at least 30 min per day, in addition to usual activities on 5 or more days of the week.

The diet and physical activity intervention is tailored to each patient based on the information collected during their baseline interview. The nutritionist meets each patient to discuss their calculated energy and nutrient requirements. Dietary recommendations are based on the information collected on weight, physical activity levels and baseline dietary intake. Energy is calculated based on actual body weight; however, 500 kcal/day reduction is advised to the overweight/obese patients to prevent or reduce weight gain. Each patient in the intervention arm receives an individualised guidebook with tips and guidelines to help adherence to the diet. The guidebook includes; a sample menu to provide an example of the amounts and type of foods that can be included for breakfast, lunch, dinner and snacks; a list of portion sizes for foods typically eaten; tips to incorporate more fruit, vegetables and fibre, and reduce total fat, saturated fat, sugar and salt; a list of healthier foods choices and a list of foods that should be chosen less frequently from all food groups; examples of healthy alternative menus for breakfast, snacks, lunch and dinner.

The physical activity intervention is also tailored to each patient based on their baseline physical activity level. As a minimum, each patient is asked to walk at a brisk pace for at least 30 minutes per day, 5 times or more per week. However, men who are already physically active are advised to increase the duration and frequency of walking each week. They are also asked to set a goal of increasing the number of steps by at least 10% every week. A pedometer is provided to each participant in an effort to encourage them to comply with the physical activity intervention and as an independent measure of physical activity levels during the intervention period.

Men in the control group will receive standard care during the intervention period but will be offered the same guidelines at the end of the 6 month intervention.

### Data collection

Data to evaluate the efficacy of the intervention are collected at baseline and at 3 and 6 months after the intervention has begun in the intervention and control group. Data are collected via interview, self administrated questionnaire, physical and biological measurements. Data collection instruments and the study timeline are summarised in Table 1. All instruments used have been previously validated and we also pre-tested them in the Northern Irish population prior to use in the study.

**Table 1 T1:** Data collection instruments at different assessment points

	Baseline	3-month follow-up	6-month follow-up
Anthropometry	**X**	**X**	**X**

FSS	**X**	**X**	**X**

FACT-P	**X**	**X**	**X**

7-DPARQ	**X**	**X**	**X**

6-min Walk Test	**X**	**X**	**X**

PSS-10	**X**	**X**	**X**

7DD	**X**	**X**	**X**

Fasting blood sample	**X**	**X**	**X**

TTM	**X**		

Questionnaire for background information	**X**		

### Primary outcomes

The three main outcomes of interest are changes in body composition, fatigue and quality of life.

#### Body Composition

Measures of body composition include percentage body fat (assessed from skin fold thickness measured at 4 sites; triceps, biceps, subscapular and suprailiac using a Harpenden Skinfold Calipers), height, (measured to the nearest centimetre using SECA Leicester Height Measure), weight (SECA 704 Electronic Column Scale), body mass index (BMI) (Kg/M^2^), waist and hip circumference as a measure of central adiposity and mid upper arm circumference as a measure of lean body mass. A standard protocol is used to conduct all anthropometric measurements [20].

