### Statistics

The data collected in the trial will be analysed based on intention to treat and lost to follow-up cases will be considered as missing observations [38]. Change over the treatment period will be calculated by subtracting the baseline value from the value at month 3 and month 6. Primary and secondary endpoints between those assigned to the intervention and control group will be compared using analysis of covariance (ANCOVA) with baseline scores included in the models as covariates. Skewed data will be log transformed prior to inclusion in the ANCOVA models. The trial outline conforms to the Consort statement guidelines.

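### The 90% power is stated for percentage change in fat mass, but the listed fat outcome is change in skinfold percentage body fat; and uncorrected arm circumference, the lean measure, contains fat

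*Protocol article*

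**What the plan says.** All references are to the protocol article.

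- **Hypothesis**: the intervention is expected to limit weight gain and the rise in body fat mass. Lean mass is not named.
- **Sample size**: "The primary endpoint used to calculate sample size was body composition". The planning source is described thus: "the mean percentage change in fat mass following ADT treatment was 9.4% (SD = 9.6"%). The trial is sized "to detect a mean percentage change in fat mass of 7.4% between the control and intervention group", with 36 per arm before a 30% allowance brings it to 47.
- **Body Composition** (under Primary outcomes): "Measures of body composition include percentage body fat (assessed from skin fold thickness measured at 4 sites"), then height, weight, BMI, waist and hip circumference, and "mid upper arm circumference as a measure of lean body mass". Neither fat mass nor fat-free mass is listed.
- **Statistics**: "Change over the treatment period will be calculated by subtracting the baseline value from the value at month 3 and month 6". Arms are compared by ANCOVA with the baseline value as covariate. Skewed data are log transformed.
- **Discussion**: the sample size is said to be adequate for a clinically relevant change in body composition.

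**The concern.** The fat outcome appears in two forms. The sample size uses relative change in fat mass (kilograms of fat, as a percentage of each man's baseline). The outcome list and the Statistics section, read together, give the absolute change in percentage body fat (percentage points). Nothing in the article links them.

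They are different quantities because percentage body fat has body weight as its denominator, and weight is expected to move differently in the two arms. The Intervention section describes an energy reduction for overweight and obese men in the intervention arm, and the Discussion expects modest weight loss there. A difference and an SD stated for one measure therefore cannot be read across to the other, and the claim of adequate size rests on that step.

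The lean measure raises a second, separate question. Arm circumference encloses subcutaneous fat as well as muscle. The intervention is meant to change fat, so the error would not be the same in both arms. Fat loss in the intervention arm could look like lean loss, and fat gain in controls could mask the lean loss that the Background attributes to ADT.

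**Working it through.** **1. Reproduce the stated figure.** Inputs from Sample size: difference 7.4, SD 9.6 (both in percent of baseline fat mass), 5% significance, 90% power. Inputs from Design: 1:1 allocation. Sidedness is not stated; two-sided reproduces the figure, whereas one-sided would need only 29 per arm.

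n per arm = 2 × (1.960 + 1.282)² × (9.6/7.4)² = 2 × 10.51 × 1.683 = 35.4, so 36. Power at 36 per arm is 90.5% (normal approximation) or 89.7% (t-test). The arithmetic is right for percentage change in fat mass.

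**2. When would the power carry over?** Suppose every man starts at 30% fat (assumed) and weight stays constant. Then 7.4% becomes 0.074 × 30 = 2.22 points and 9.6% becomes 0.096 × 30 = 2.88 points. The ratio is unchanged (2.22/2.88 = 7.4/9.6 = 0.771), and so is the power. The carry-over thus needs constant weight and a skinfold measure with the same relative variability. The article supports neither.

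**3. Let weight move.** Assume an 85 kg man with 30% fat: 25.5 kg fat and 59.5 kg lean.
- Fat +9.4%, lean constant: fat 27.9 kg, weight 87.4 kg, body fat 31.9%. That is +1.9 points, or 6.4% relative.
- Fat +9.4%, lean −3%: +2.6 points, or 8.6% relative.

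If weight changes only through fat, a baseline fraction f and relative fat change r give a change of f(1 + r)/(1 + f r) − f. For f = 0.30, controls at r = 0.094 move 1.92 points and intervention men at r = 0.020 move 0.42, a contrast of 1.50 points instead of 2.22. At baselines of 25% and 35% the contrast is 1.35 and 1.62 points, against 1.85 and 2.59 at constant weight. The smaller contrast is not by itself a loss of power, since the SD would change too. It shows only that the planning figures do not transfer.

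**4. Range of power for percentage body fat.** The article gives neither a baseline nor an SD for this measure, so both are assumed. At 30% baseline, constant weight and a difference of 2.22 points, two-sided 5%:

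| Assumed SD of change (points) | Power at 36 per arm | n per arm for 90% |
|---|---|---|
| 2.5 | 96.5% | 27 |
| 3.0 | 88.1% | 39 |
| 3.5 | 76.8% | 53 |
| 4.0 | 65.3% | 69 |

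Over the same SDs, power runs from 88.1% down to 50.1% at 25% baseline, and from 99.3% down to 78.4% at 35%.

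**5. Arm circumference.** Treating the arm as a cylinder, muscle circumference = arm circumference − π × triceps skinfold. An assumed 2 mm skinfold change with muscle unchanged moves arm circumference by π × 0.2 cm = 0.63 cm, in the direction of the fat change.

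**The case against.** A reader might infer that neither fat mass nor lean mass is tested at all. The article does not support that. Weight and skinfolds are taken at baseline, 3 and 6 months, so fat mass and fat-free mass can be calculated. The list of measures is worded as inclusive, and a fuller protocol or analysis plan may define them. Arm circumference is openly labelled a measure of lean mass, so lean mass is tested, though by a weak proxy. This limits the claim but does not remove it: that a variable can be derived does not show it is planned, and the list does name another derived index, BMI.

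The Statistics section also does more than take raw differences. It adjusts for baseline and allows logs for skewed data, which comes close to a relative-change analysis. That stands, but the log step depends on skewness and is not tied to fat.

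Lean mass is in neither the hypothesis nor the sample size, so the arm-circumference point is no sizing mismatch. That is correct, and it is kept separate here as a question of measurement.

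Finally, the article calls the study exploratory and says formal power calculations are difficult. Even so, it states 90% power and later relies on the size being sufficient.

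**Conclusion.** The point holds in limited form. The sample-size arithmetic is correct, but the 90% belongs to relative change in fat mass, which the article does not say it will analyse. For the listed outcome, change in skinfold percentage body fat, power is undetermined: about 97% to 65% at 36 per arm for assumed SDs of 2.5 to 4.0 points, with 30% baseline fat and constant weight also assumed.

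It would be tempting to conclude that the trial is underpowered. The article does not show this; without an SD for the measure, power may be higher or lower than stated.

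On lean mass, uncorrected arm circumference mixes fat with muscle in a trial meant to change fat, so the comparison as written is open to bias. A result with the wrong sign is possible but not shown. The 0.63 cm figure rests on an assumed 2 mm skinfold change, and nothing in the article indicates whether that would outweigh a true change in muscle.

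**What to change.** **Fat.** Do one of the following, and state it before the data are analysed:
- Derive fat mass = weight × percentage body fat/100 at each visit. Name its relative change at 6 months as the body-composition primary, analysed as log fat mass with log baseline fat mass as covariate and back-transformed to a percentage difference. The planning contrast (controls +9.4%, intervention +2.0%) is then a ratio of 1.020/1.094 = 0.932. State that the SD of 9.6% is assumed to apply to skinfold-derived fat mass; the article does not say how the cited study measured fat.
- Or keep percentage body fat as the outcome and restate the power with a difference and SD for that measure.

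**Lean.** Report fat-free mass (weight minus fat mass) and arm muscle circumference (mid upper arm circumference minus π × triceps skinfold) as the lean measures. Keep raw arm circumference as descriptive only.

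**Cost.** No new data: weight, the skinfolds and arm circumference are already collected at all three visits. The price is a few derived variables, which carry skinfold measurement error, and revised wording in Sample size, Body Composition and Statistics. Fixing the choice in advance also matters because several body measures are listed and, as Quality control says, the measurer is not masked.
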